### **13.8.3 Reporting of Adverse Clinical Laboratory Trends**

Six months after the first subject is enrolled in the study, and at the end of each 6 month period thereafter, the DCC will:

- Make a "snapshot" copy of the study's clinical laboratory data.
- Perform an appropriate statistical analysis of clinical laboratory change-from-baseline data for each clinical laboratory evaluation obtained in this study.
- Perform an appropriate statistical test of  $H_0$ : (The mean [or median, or proportion, as appropriate] change-from-baseline of the clinical laboratory values for the active treatment group is the same as for the control group), vs.  $H_a$ : (The mean [or median, or proportion] change-from-baseline in the active treatment group is "worse" than for the control group). The meaning of "worse" depends upon the specific clinical lab measurement. The test statistic p-value is not adjusted for multiplicity.
- If the hypothesis tests p-value is less than the critical value shown in Table 12, the DCC will conduct further statistical analyses as indicated by the circumstances and highlight this finding in the semi-annual DSMB report.
- Collaborate with the PI to incorporate the results into the study's semi-annual report to the DSMB and the NHLBI Project Officer.
- A copy of the study's semi-annual report will be submitted to the IND Holder's IRB. Measures will be taken to ensure that the CI and study coordinator at that site remain blinded to their subject's treatment.

**Table 12. Summary of Procedures and Timing for Alerting the DSMB and NHLBI Project Officer of Possible Serious Safety Issues**

| Situation or Event                 | Summary of Procedure (See text for details.)                                                                                                                                                                                                                                                                                                  | Critical Value for DSMB “Alert”           |
|-------------------------------------------|------------------------------------------------------------------------------------------------------------------------------------------------------------------------------------------------------------------------------------------------------------------------------------------------------------------------------------------------------|--------------------------------------------------|
| Unexpected SAEs                           | Clinical investigator notifies DCC SAE Regulatory Specialist and PI.
Clinical investigator, DCC SAE Regulatory Specialist and PI prepare report using FDA forms and submit report to DSMB, NHLBI Project Officer, IRBs, study investigators. Report:
Fatal or life-threatening: within 7 calendar days.
Otherwise: within 15 calendar days. | Alert all cases.                                 |
| Serious Bleeding Events, other than above | Clinical investigator notifies DCC SAE Regulatory Specialist and PI.
Clinical investigator, DCC SAE Regulatory Specialist and PI prepare report and submit report to DSMB and NHLBI Project Officer within 15 calendar days                                                                                                                       | Alert all cases.                                 |
| All SAEs                                  | DCC performs quarterly analyses of MedDRA-coded SAEs, tabulates subjects with SAEs classified by highest-level MedDRA term. Report only when $p <$ critical value and active treatment group has higher AE rate.                                                                                                                                     | $p < 0.01$
$p$ not adjusted for multiplicity  |
| Adverse Events (all)                      | DCC performs semi-annual analyses of MedDRA-coded AEs, tabulates subjects with AEs classified by highest-level MedDRA term. Report every 6 months. Alert only when FET $p <$ critical value and active treatment group has higher AE rate.                                                                                                           | $p < 0.01$
$p$ not adjusted for multiplicity  |
| Adverse Clinical Lab Trends               | DCC performs semi-annual analyses of clinical lab change-from-baseline using analyses appropriate for the data type. Report every 6 months. Alert only when $p <$ critical value and change is in “adverse” direction.                                                                                                                               | $p < 0.005$
$p$ not adjusted for multiplicity |

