### **13.6.2 IND Safety Reporting to the FDA**

Because this study will be conducted under an IND, U.S. Government regulations 21CFR, Part 312.32 require the issuance of an IND Safety Report to the Food and Drug Administration (FDA) for all “serious” adverse events that are “unexpected” and for which there is a “reasonable possibility that the experience may have been caused by the drug.” Such serious events that are characterized as fatal or life-threatening must be reported to the FDA within 7 calendar days of the sponsor’s initial receipt of the information, whereas non-fatal and non-life threatening events must be reported within 15 calendar days.

The list in Table 11 identifies potentially serious adverse events that are “expected” based on the underlying disease, sickle cell anemia, or on the right heart catheterization procedure. Section 13.7.2 includes additional expected SAEs based on PH and study procedures. No expedited IND Safety Report is required if the event is considered to be expected based either on the sildenafil product label, the underlying disease states (i.e., PH or sickle cell disease), or the study procedures. Additionally, a serious adverse event requires an expedited report to the FDA only if it is considered to be at least possibly related to study drug.

The Product Safety Team will issue IND Safety Reports to NHLBI for all unexpected, serious adverse events that are believed to be at least possibly related to study drug. In compliance with FDA and National Institutes of Health (NIH) regulations, the Product Safety Team will prepare a collaborative report of these qualifying SAEs using the current version of the FDA MedWatch reporting form. The form will be sent to NHLBI for review and submission to the FDA. When an SAE requiring an IND Safety Report has not resolved by the report deadline, NHLBI will send the report to the FDA, and the Product Safety Team will work with the CI’s to gather follow-up reports on the event.

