### **13.7.2 SAEs that Require Expedited Reporting to the IRB**

The following serious adverse events will be listed in the consent and reported to the local IRB within 7 days of a death or other life threatening event or 15 days of any other serious adverse event as outlined in the Interim Guidelines for Adverse Event Reporting. Other SAEs not noted herein will be reported to local IRBs per the guidelines of each IRB.

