#### **Hematology (Sickle Cell Anemia)**

- Priapism requiring medical or surgical intervention
- Acute chest syndrome/pneumonia requiring simple or exchange transfusion, admission and antibiotic therapy (not mechanical ventilation)
- Infections from bacteria, viruses, protozoa and fungi requiring vasopressor support or hospital admission
- Avascular necrosis of the femoral head requiring surgical intervention

- Bleeding requiring transfusion
- Major bleeding complication including intracerebral hemorrhage, stroke or GI bleed
- Sustained thrombocytopenia or neutropenia
- New leg ulcers requiring surgical intervention
- Greater than two admissions for vaso-occlusive crisis per week for two sequential weeks
- Retinal detachment or vitreous bleeding
- Pulmonary embolism
- All hospitalizations for medical indications (with the exception of hospitalizations for vaso-occlusive crises – per Section 13.7.1)

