## **13.8 Reporting of Serious Safety Issues to the DSMB; Suspension Guidelines**

Serious safety issues that arise in this study will be brought to the attention of the Data and Safety Monitoring Board (DSMB), which will make recommendations to the National Heart, Lung, and Blood Institute (NHLBI) regarding possible suspension or termination of the study. The NHLBI will consider the DSMB's recommendations, determine an appropriate action and notify the Data Coordinating Center (DCC). The DCC will notify all participating investigators, who will implement the actions directed by the NHLBI. This section defines "serious safety issues" and describes procedures for bringing them to the attention of the DSMB.

The DCC or PI will make the following types of reports that can alert the DSMB to a potential safety issue:

- Ad hoc reports of unexpected serious adverse events and those serious adverse events associated with major bleeding that are made within 7 or 15 calendar days, as specified in subsequent paragraphs.

- Reports of quarterly statistical analyses of all serious adverse events. The DCC will make such analyses quarterly, but files a report to the DSMB only when analyses indicate that a safety issue has arisen, as defined by the “alert” criteria.
- Reports of semi-annual DCC analyses of all adverse events and of adverse clinical laboratory trends. These reports will highlight any safety issues revealed by the analyses that meet the “alert” criteria.

The DCC will submit the DSMB report to the Chair of the DSMB Subcommittee appointed to monitor this study and to the NHLBI Project Officer and will submit the unexpected SAE report to all study investigators. Each CI will submit the unexpected SAE report to the local Institutional Review Board (IRB) and other local authorities in accordance with the institution’s regulations.

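### Table 12 sets no shorter DSMB reporting limit for a fatal or life-threatening serious bleed that is judged expected

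*Protocol*

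**What the plan says.** Table 12, which closes Section 13.8.3, lists what must be brought to the DSMB and when.

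- **Unexpected SAEs.** The limit depends on outcome: "Fatal or life-threatening: within 7 calendar days", and 15 calendar days for the rest.
- **"Serious Bleeding Events, other than above".** Every case triggers an alert, but there is one limit only: "prepare report and submit report to DSMB and NHLBI Project Officer within 15 calendar days".
- **All SAEs and all AEs.** These are analysed quarterly and every six months respectively. An alert follows only if p < 0.01 with a higher rate on active treatment.

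Three other sections bear on the bleeding row.

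- Section 13.8 introduces ad hoc reports of unexpected SAEs together with "those serious adverse events associated with major bleeding that are made within 7 or 15 calendar days, as specified in subsequent paragraphs".
- Section 13.7.2 requires listed SAEs to be "reported to the local IRB within 7 days of a death or other life threatening event", with 15 days for other serious events. Its sickle cell list contains "Major bleeding complication including intracerebral hemorrhage, stroke or GI bleed", and also bleeding that needs transfusion.
- Section 13.6.2, on what counts as expected, states: "Section 13.7.2 includes additional expected SAEs based on PH and study procedures". It also treats as expected anything covered by the product label, the underlying diseases or the study procedures.

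**The concern.** Bleeding is the one harm that Table 12 singles out for case-by-case alert even when it is not unexpected. Within that row, however, the gravest cases get the same time limit as the least grave. For a fatal or life-threatening bleed judged expected, the body that advises on suspending the trial could be told later than a local IRB, with both deadlines met. The limit for reporting a death to the DSMB would also turn on a case-by-case judgement of expectedness.

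The stake is how promptly the DSMB, and through it NHLBI, can consider such an event. Endpoints, the analysis and the type I error rate are not affected.

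**Working it through.** No figure in the plan needs reproducing. The check is a comparison of time limits, followed by a search for any faster route.

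**Step 1. Limits side by side**

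| Event | DSMB limit (Table 12) | Local IRB limit (13.7.2) | Difference |
|---|---|---|---|
| Major bleed, fatal or life-threatening, judged unexpected | 7 days | 7 days | 7 − 7 = 0 |
| Major bleed, fatal or life-threatening, judged expected | 15 days | 7 days | 15 − 7 = 8 |
| Major bleed, serious but neither, judged expected | 15 days | 15 days | 15 − 15 = 0 |

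Only the middle line is out of step. Within Table 12 itself, the same outcome carries 7 days or 15 days according to expectedness alone, again a difference of 8 days.

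**Step 2. Does the text of Section 13.8 supply a shorter limit?** It names two possible limits for two classes of event taken together and leaves the allocation to later paragraphs. Sections 13.8.1 (SAE tables), 13.8.2 (all AEs) and 13.8.3 (laboratory trends) say nothing specific to bleeding. Table 12 in turn refers the reader to the text for details. The undivided 15-day cell is therefore the only specification.

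**Step 3. Is there another expedited route to the DSMB?** Section 13.6.2 requires no expedited IND safety report for an expected event, so the 7-day FDA route does not apply. The remaining DSMB triggers are the periodic analyses. The protocol gives no faster DSMB route for an expected bleed.

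**Step 4. Can a major bleed be judged expected?** The bleeding row covers only serious bleeds outside the unexpected row, so it presupposes that some are expected. Whether a particular major bleed would be is left open:

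- Section 13.6.2 points to Section 13.7.2 for further expected SAEs, but describes them as based on PH and study procedures. The major-bleeding item stands under the sickle cell heading.
- Table 11, the list of sickle cell and catheterization events, names neither intracerebral hemorrhage, stroke, GI bleeding nor major bleeding.
- The product label may also decide the matter. Section 12.3.2.3 mentions cerebrovascular hemorrhage among post-marketing reports, but the label is not in the document.
- Section 13.6.1 gives the decision to the Product Safety Team, case by case. No section says that a fatal outcome makes an otherwise expected event unexpected.

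The middle line of the table is therefore possible under the protocol, but not certain to arise.

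**The case against.** The case for leaving the row alone has real substance.

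- **Different recipients.** Section 13.7.2 governs IRBs and Table 12 governs the DSMB. Nothing in the protocol requires the DSMB to hear no later than an IRB. Other expected SAEs reach the DSMB only through periodic statistics, so the bleeding row already adds protection. This stands, and it makes the point an improvement to the design rather than the correction of a breach. It does not explain why the row drops the outcome split used directly above it.
- **Section 13.8 can be read consistently with Table 12.** A reader might infer that the two contradict each other. They do not have to: the sentence covers unexpected SAEs and bleeding SAEs jointly, so 7 days may belong only to fatal or life-threatening unexpected SAEs and 15 to the rest. What remains is a cross-reference that leads nowhere.
- **Not every fatal bleed falls in the 15-day row.** A reader might infer this from the listing in Section 13.7.2. As shown above, the documents do not settle expectedness for major bleeding, and a bleed judged unexpected already has a 7-day limit.
- **The delay should not be turned into patients.** A reader might multiply 8 days by the planned accrual rate and call the result additional exposure. No section says that one DSMB report pauses enrolment: the DSMB recommends and NHLBI decides. The two limits are also maxima, and they need not start together, because Section 13.7.2 counts from the event while the bleeding row names no start point.
- **Other safeguards operate.** The coordinating center hears of every SAE no later than the next business day after the investigator learns of it, and its safety staff consult the medical monitor (Section 13.6.1). Section 7.1 lists major bleeding as a reason to discontinue the affected subject's therapy. The DSMB's charter (Section 13.10.1), which is not shown, may address deaths. These points stand, and they place any delay in the step to the DSMB and NHLBI, not in site reporting.

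**Conclusion.** The point holds in a narrow form. Table 12 has no shorter limit for fatal or life-threatening cases in the bleeding row, and no other section supplies one. If such a bleed is judged expected, the outer limit to the DSMB is 15 days, against 7 days to the local IRB and 7 days to the DSMB for an unexpected fatal SAE.

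The 8-day difference is between permitted maxima and predicts no actual delay. The conclusion assumes that the Product Safety Team may class a major bleed as expected, and that the DSMB charter sets no tighter rule. If either assumption fails, the practical gap closes, although the table would still be unclear. The matter is minor: an inexpensive improvement in safety reporting.

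**What to change.** Split the bleeding row of Table 12 in the same way as the row above it: fatal or life-threatening events within 7 calendar days, other serious bleeds within 15. The limit then no longer depends on expectedness, and the middle line of the comparison becomes 7 − 7 = 0. The reference in Section 13.8 should point to Table 12, so that Section 13.8, Section 13.7.2 and the table are reconciled.

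The cost is one table cell, one corrected cross-reference and a few reports prepared sooner. Because the coordinating center already receives SAE reports no later than the next business day, no new data collection is needed. Nothing changes in subject management, the endpoints or the analysis.

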### 13.9 Pregnancy Reporting

Because of potential adverse effects on the fetus, pregnant subjects will be excluded from the study. Female subjects who are pubertal will be regularly assessed throughout the study. In the event of a positive pregnancy test, the subject will be immediately informed of this result and will have sildenafil treatment discontinued.

The investigator, or his/her designee, will collect pregnancy information on any female who becomes pregnant while participating in this study. The investigator or his/her designee will record pregnancy information on the appropriate form and submit it to the DCC Product Safety Associate within 2 weeks of learning of a subject’s pregnancy. The

subject will also be followed to determine the outcome of the pregnancy. Information on the status of the mother and child will also be reported to the DCC. Generally follow-up will be no longer than 6 to 8 weeks following the estimated delivery date. Any premature termination of the pregnancy will be reported.

While pregnancy itself is not considered to be an AE or SAE, any pregnancy complication, elective termination of a pregnancy for medical reasons, or spontaneous abortion will be recorded as an AE or a SAE, as appropriate.

## **13.10 Clinical and Safety Monitoring**

### **13.10.1 Subject Safety Monitoring**

The Data and Safety Monitoring Board (DSMB) has been appointed by and is responsible to NHLBI. The DSMB has adopted a written charter that has been approved by NHLBI and will govern its activities. The DSMB will decide how often they need to review the safety data for each protocol. The DCC will provide a report to the DSMB approximately 2 weeks prior to each scheduled DSMB meeting. This report will consist of relevant safety information. Upon review of the safety data, the DSMB will make a recommendation to continue the trial or stop it due to safety concerns.

### **13.10.2 Clinical Monitoring Plan**

A study coordinator from the DCC will assess overall enrollment and compliance with the clinical protocol at all participating sites. A trained clinical research associate (CRA) will visit the sites once every year for the duration of the trial. The CRA will focus on compliance with Good Clinical Practice and data quality and will provide feedback to the sites on how well they are capturing and entering their data.

### **13.10.3 Plan for Reporting Protocol Violations/Deviations**

All protocol violations/deviations will be reported on the DCC Protocol Deviation/Violation Form. This form asks for a description of the event, any corrective action taken, and the final disposition of the event.

## **14 COMPENSATION**

Each study site will determine compensation for subjects participating at that site. The terms of the compensation will be approved by that site's governing IRB.

## **15 STUDY CONDUCT**

This protocol has been filed under an Investigational New Drug (IND) application with the US Food and Drug Administration (FDA) and will be conducted in accordance with "good clinical practice" (GCP), all applicable US regulatory requirements, and where

applicable, the UK Medicines for Human Use (Clinical Trials) Regulations 2004 (SI 2004/1031) and the European Clinical Trials Directive 2001/20/EC (EUCTD).

## **18 APPENDICES**

**Appendix A: Echocardiographic parameters**

---

---

|                                  |                                                |
|----------------------------------|------------------------------------------------|
| LV Structure
and Function     | LVED size (mm)                                 |
|                                  | LVES size (mm)                                 |
|                                  | Septal thickness (mm)                          |
|                                  | PW thickness (mm)                              |
|                                  | LVMI (m/h)                                     |
|                                  | LVEF (%)                                       |
| LV Diastolic
Function         | Left atrial area (cm  )            |
|                                  | Max LA vol/BSA (ml/m  )            |
|                                  | Peak E velocity (m/s)                          |
|                                  | Peak A velocity (m/s)                          |
|                                  | E/A ratio                                      |
|                                  | Deceleration time (msec)                       |
|                                  | Isovolumic relaxation time (msec)              |
|                                  | Pulmonary vein flow                            |
|                                  | Tissue Doppler of the septum and lateral walls |
| Right Heart Size
and Function | Right atrial area (cm  )           |
|                                  | RV end diastolic area (cm  )       |
|                                  | RV end systolic area (cm  )        |
|                                  | RV area change (%)                             |
|                                  | RV:LV diastolic area ratio                     |
|                                  | Tricuspid regurgitant jet velocity (m/s)       |
| Valvular Function                |                                                |

---

**Appendix B: Patient History Intake Document**

Date of visit:  
 History and Physical exam and significant findings  
 Chief Complaint:  
 History of the Present Illness:  
 Past Medical History / Review of Systems:  
 Allergies:

**HOSPITALIZATIONS**

Date of last hospitalization:  
 Reason for admission:

Number of hospitalizations in last year:

